#### Confidentiality and coding

The server hosting the EDC system and the database is kept in a locked server-room. Only the system administrators have direct access to the server and back-up tapes. A role concept with personal passwords (site investigator, statistician, monitor, administrator etc.) regulates permission for each user to use the system and database as he/she requires. Authorized to enter data into the eCRF are the local trial team staff according to the database access list. The local project leader is responsible for proper training and instruction of the trial personnel filling data into the eCRF. Study-related data of the patient will be collected in a coded manner. The names of the patients will not be disclosed. A code (unique, consecutively numbered per center) will be attributed to each patient registered. All data entered into the CRFs are transferred to the database using Transport Layer Security (TLS) encryption. Each data point has attributes attached to it identifying the user who entered it with the exact time and date. Retrospective alterations of data in the database are recorded in an audit table. Time, table, data field and altered value, and the person are recorded (audit trail). A multi-level back-up system is implemented. Back-ups of the whole system including the database are run internally several times per day and on external harddrives once a day. The back-up tapes are stored in a secure place in a different building.

#### Biological material

Biological material in this project will be coded using a barcode system that will be linked to the patient ID and sampling attributes. Biological material is appropriately stored in a restricted area only accessible to authorized personnel. CSF samples from local sites will be shipped to Research Biobanking Service Center (RBSC), University Hospital Zurich, Zurich, Switzerland.

#### Retention and destruction of study data and biological material

At final analyses, data files will be extracted from the database into the statistical software R to be analyzed. After database lock, the status of the database is recorded in special archive tables. The sponsor will keep the Trial Master File, the extracted data, the meta data and final reports for at least 10 years. Each site will archive its study documents for at least 10 years. Leftover CSF samples will be stored for a maximum time period of 10 years. At the end of this period they will be destroyed according to local law and regulations.

### Sample size

The primary objective of the study focuses on patients included with EVD (EVD cohort) while secondary objectives also consider patients with LD (LD cohort) and patients irrespective of any drainage system (full cohort). The sample size estimation is based on an anticipated effect size of 0.1, a power of 90% and accounts for between-site variability using a generalized linear mixed model. This calculation results in a minimum of 6 participating study sites and 30 patients per site with an EVD. Considering an anticipated drop-out rate of 15% and heterogenous recruitment rates at the sites, we plan to include 8 sites and a maximal study population of 250 patients with EVD. Based on our clinical experience, we assume that only every second subject receives an EVD. Thus, we assume to include a maximum of 500 subjects. The recruitment will be stopped as soon as 250 patients with EVD are included.

### Statistical analysis

Statistical analyses will be performed in R in an R studio environment on a Mac computer operating system [15]. The entire statistical code will be written by two authors (KA and [name]). The reviewing statistician (UH) will have an overview of the entire code. A second review statistician will independently reproduce the primary analyses. No interim analysis will be performed. The final analysis will be conducted after completion of the study, i.e. when every patient has reached the 12 weeks follow-up, and data has been cleaned by the central data monitor. For analysis, the study population will be divided into the following three populations: EVD cohort (at least one CSF-sampling via an EVD), LD cohort (at least one CSF-sampling via an LD), full cohort (all included patients, irrespective of their CSF-sampling status). The null hypothesis is that there is no association between the concentration of EVD based CSF-Hb and the occurrence of SAH-SBI during the first 14 days post-SAH in the EVD cohort. The confirmatory alternative hypothesis is that there is an association between the two. The primary analysis evaluates the strength of association between SAH-SBI (dependent binary variable) and EVD based CSF-Hb (independent continuous variable) in the EVD cohort based on a generalized additive model (GAM) with day post-SAH as continuous covariable (non-linear spline-fit with 4 knots), and repeated observations in the same patients over time and each study site accounted for with random intercepts. The likelihood ratio test *p*-value will be used to test the null hypothesis of no effect of the biomarker at a 5% significance level. In the primary analysis, no adjustment of the significance level for multiple testing is needed. Detailed description on summary statistics, secondary and safety endpoint analyses can be found online in the statistical analysis plan (10.5281/zenodo.5556317). For secondary analyses, no level of statistical significance will be defined. Instead, the results of secondary analyses will be interpreted based on the level of evidence (*p* < 0.001: very strong evidence; *p* < 0.01: strong evidence; *p* < 0.05 evidence; *p* < 0.1 weak evidence; *p* > 0.1: no evidence [16]) and confidence intervals will be provided. No confirmatory claims will be based on the secondary analyses. The results of the study will be reported according to STROBE guidelines for reporting of observational research [17].

### Ethics and dissemination

The HeMoVal study is conducted in accordance with the Declaration of Helsinki and national and international standards of ICH-GCP E6(R2). Potential participants or their legal representatives receive detailed written and oral information on the study procedures and all participants or their legal representatives provide written informed consent. The study protocol will be approved by the local ethics committees of all participating study sites. To date, the study protocol has been approved by the ethics committee of the Canton of Zurich, Switzerland (KEK 2021–01023) for Zurich (CH), Aarau (CH), and St. Gallen (CH). The primary and secondary results of this study will be published in peer-reviewed journals. Authors of these publications are persons who planned and/or conducted the study and/or did parts of the statistical analysis.

### Study registration

ClinicalTrials.gov Identifier NCT04998370. Date of registration: August 10, 2021.

### Current status of the study

Recruitment for the HeMoVal study is currently starting at multiple centers across Switzerland, Germany and the Netherlands. At the University Hospital of Zurich (Switzerland) the recruitment started on August 15, 2021, and at the Kantonsspital Aarau (Switzerland) on August 25, 2021. At the time of submission of this protocol, 21 patients have been enrolled in the HeMoVal study.

## Discussion

Preclinical studies provide a strong rationale for a causal pathophysiological link between CSF-Hb and SAH-SBI [12–14]. Also, CSF-Hb demonstrated to be a promising clinical biomarker to monitor for SAH-SBI in a prospective single-center observational study [12]. The primary objective of the herein described prospective international multicenter observational cohort study is to externally validate the positive association between EVD based CSF-Hb and SAH-SBI during the first 14 days post-SAH. Secondary objectives include the assessment of the discrimination ability of EVD based CSF-Hb for SAH-SBI and the definition of a clinically relevant range of EVD based CSF-Hb toxicity. Additionally, LD-based CSF-Hb will be assessed for its association with and discriminatory ability for SAH-SBI.

There is considerable heterogeneity in the use of the terms aVSP, DCI and DIND in both literature and clinical practice [18]. The composite outcome SAH-SBI constitutes the primary endpoint of the HeMoVal study, conceptualizing the pathophysiological and clinical interconnection between aVSP, DCI and DIND, thus increasing statistical power. The concept of SAH-SBI is strengthened by the previous finding of a dose-dependent relation between EVD based CSF-Hb and aVSP, DCI and DIND with increasing toxicity ranges [12]. As secondary endpoints, aVSP, DCI and DIND will be assessed individually. The strictly delineated definition of these endpoints based on angiographic vessel narrowing (aVSP), perfusion deficit/infarction (DCI) or clinical deterioration (DIND) empowers conclusions regarding CSF-Hb toxicity range and intervention thresholds.

The HeMoVal study will enroll all patients who are diagnosed with aSAH at admission, thus ensuring that start of CSF sampling from a newly introduced EVD or LD is possible at each day of the 14-day monitoring period. For the statistical analysis, the cohort will be stratified into an EVD cohort (at least one CSF sample obtained via an EVD), LD cohort (at least one CSF sample obtained via an LD), and a full cohort (all patients admitted with an aSAH). Distinguishing between EVD and LD cohorts anticipates potential differences in the temporal profiles of EVD and LD based CSF-Hb, and hence their association to and discrimination ability for SAH-SBI. Despite the anatomical communication between the intraventricular and lumbar CSF spaces, substantial differences in the protein levels of samples obtained from the two compartments were described in patients with multiple sclerosis [19]. The full cohort serves as reference for the generalizability of the finding in the EVD and LD cohort to the overall aSAH population.

The strength of association between CSF-Hb and SAH-SBI, aVSP, DCI, and DIND will be quantified using a GAM. GAMs blend properties of generalized linear models with additive models [20]. The data structure of the HeMoVal study is characterized by repeated CSF-Hb measurements and clinical assessments (aVSP, DCI, DIND, and hence the composite outcome SAH-SBI) in the same subjects during the 14 day monitoring period, for which we will adjust with a random intercept. In the same way, there will be adjustment for potential intracluster correlation per study site. In addition, based on the results of our pilot study, we expect a non-linear relation of SAH-SBI, aVSP, DCI, and DIND to the day post-SAH with a peak between post-SAH day 8 and 12 [12]. A GAM provides the flexibility to incorporate these properties, including smooth functions of covariates, while maintaining some degree of explainability [20].

The collection of CSF samples for the HeMoVal study is a manipulation at the closed EVD/LD drainage system, which may raise concerns about an increased risk for CSF infections. Reported infection rates of EVD/LD systems in clinical routine range from 0 to 32%. However, rates around 10% are usually described [21–23]. Since the introduction of antimicrobial-coated catheters, infection rates of less than 2% have been reported at many centers [24–29]. The single most important risk factor for CSF infection in patients with EVD/LD is the duration of external CSF diversion [21, 23, 30–32]. This factor is not influenced by the HeMoVal study, since the indications for insertion and removal of CSF diversion devices are made independent of the study exclusively based on clinical criteria assessed by the independent treating physician (e.g., increased intracranial pressure, need for pressure monitoring). The HeMoVal study increases the number of manipulations of the EVD/LD system compared to clinical routine due to the daily sampling regimen. Evidence regarding the existence, strength, and causality of an association between such manipulations and the incidence of CSF infections is sparse and inconclusive [21, 23, 30–39], but theoretically an increased risk of infection with each manipulation must be assumed. However, strict adherence to aseptic techniques limits this risk to an absolute minimum [40–42]. In a prospective single center observational study involving 47 patients, adhering to the same protocol as the HeMoVal study, only one patient (2.1%) developed CSF infection [12]. This lies in the lower range of recent reports on the incidence of CSF infections in patients with EVD/LD [24–29]. We therefore consider the additional risk of CSF infection due to repetitive sampling under aseptic measures in this study to be minimal. However, CSF infection is included as a safety endpoint in the assessment during the monitoring period*.* Further, we don’t expect an increased risk of symptomatic CSF overdrainage due to the sampling regimen in the HeMoVal study, since the collected 2 ml of CSF per day represent only a fraction of the regular hourly drainage volume needed for the treatment of posthemorrhagic hydrocephalus [22] and because the total daily drainage volume remains unchanged. Overall, we consider that the potential scientific insights and clinical implications of the HeMoVal study clearly outweigh its risk.

In this study, a timed imaging protocol was deliberately avoided since it would have had to be performed at high frequency due to the variability of the temporal occurrence of aVSP and DCI and would therefore have been associated with an unacceptable additional burden for the patients (e.g., radiation exposure during CTA, transport risk of intubated patients). Moreover, it would not have been a compelling substitute for clinically indicated imaging in the setting of neurologic deterioration. Thus, in the HeMoVal study, we follow the real clinical situation with imaging according to clinical indication, which increases the variability of the results, but also their generalizability.

The HeMoVal study has the potential to strengthen the evidence for a positive association between CSF-Hb levels and the occurrence of SAH-SBI. In the future, CSF-Hb may serve as a biomarker to monitor for SAH-SBI. CSF processing and photospectrometry based measurements constitute easy to conduct procedures, which could be readily implemented as point-of-care test. The HeMoVal study is intended to provide generalizable data on the discrimination ability of CSF-Hb for SAH-SBI and thus to provide the basis to define an intervention threshold. Final choice on a clinical intervention threshold will additionally depend on the individual burden and the economic costs associated with false-positive and false-negative results.

Given the hypothesized causal pathophysiological link, CSF-Hb also represents a potential drug target. Targeting CSF-Hb through intrathecal application of the Hb-scavenger haptoglobin offers both preventive and therapeutic potential [12, 13]. By complexation, haptoglobin was shown to compartmentalize cell-free Hb in the CSF space, thereby inhibiting Hb delocalization into the brain parenchyma or smooth muscle cell layer of cerebral arteries [13]. Both ex vivo and in vivo, haptoglobin exhibited an anti-vasospastic effect on cerebral arteries [12, 13]. Haptoglobin also protected from lipid-peroxidation in an ex vivo assay for quantification of the oxidative potential [12]. The HeMoVal study will provide more generalizable information on the clinically relevant toxicity range of EVD and LD based CSF-Hb through ROC analyses for SAH-SBI, aVSP, DCI, and DIND. Those results are expected to inform the development of haptoglobin as a CSF-Hb targeting therapeutic in patients after aSAH.

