#### Secondary objectives

The secondary objectives are to investigate:Temporal profiles and dependence of EVD and lumbar drain (LD) based CSF-Hb:i.The temporal profile (day 1 to day 14 post-SAH) of EVD based CSF-Hb in the EVD cohort.ii.The temporal profile (day 1 to day 14 post-SAH) of LD based CSF-Hb in the LD cohort.iii.Difference (per day and overall) between EVD and LD based CSF-Hb from day 1 to day 14 post-SAH.iv.The strength of association between EVD based CSF-Hb (measured in the morning of day 1 to 14 post-SAH) and aneurysm location (assessed at study inclusion), hematoma volume (assessed at study inclusion), presence of intraventricular hemorrhage (assessed at study inclusion) and day post-SAH in the EVD cohort.v.The strength of association between LD based CSF-Hb (measured in the morning of day 1 to 14 post-SAH) and aneurysm location (assessed at study inclusion), hematoma volume (assessed at study inclusion), presence of intraventricular hemorrhage (assessed at study inclusion) and day post-SAH in the LD cohort.EVD based CSF-Hb and SAH-SBI, aVSP, DCI, and DIND in the EVD cohort:i.The temporal profiles (day 1 to day 14 post-SAH) of SAH-SBI, aVSP, DCI, and DIND in the EVD cohort.ii.The temporal profiles (day 1 to day 14 post-SAH) of EVD based CSF-Hb stratified by the presence or absence of SAH-SBI, aVSP, DCI, or DIND in the EVD cohort.iii.The strength of association between EVD based CSF-Hb (measured in the morning) and aVSP, DCI, and DIND (assessed in the afternoon of the same day) during the first 14 days post-SAH in the EVD cohort.iv.The discrimination ability of EVD based CSF-Hb (measured in the morning) for SAH-SBI, aVSP, DCI, and DIND (assessed in the afternoon of the same day) during the first 14 days post-SAH in the EVD cohort.v.The discrimination ability of EVD based CSF-Hb (measured in the morning) for the first occurence of SAH-SBI, aVSP, DCI, and DIND (assessed in the afternoon of the same day) during the first 14 days post-SAH in the EVD cohort.vi.The discrimination ability of EVD based CSF-Hb (measured in the morning of day X) for the first occurence of SAH-SBI, aVSP, DCI, and DIND (assessed in the afternoon of day X + 1) during the first 14 days post-SAH in the EVD cohort.vii.The discrimination ability of EVD based CSF-Hb (measured in the morning) for SAH-SBI, aVSP, DCI, and DIND (assessed in the afternoon of the same day) during day 4 and day 14 post-SAH in the EVD cohort.LD based CSF-Hb and SAH-SBI, aVSP, DCI, and DIND in the LD cohort:i.The temporal profiles (day 1 to day 14 post-SAH) of SAH-SBI, aVSP, DCI, and DIND in the LD cohort.ii.The temporal profiles (day 1 to day 14 post-SAH) of LD based CSF-Hb stratified by the presence or absence of SAH-SBI, aVSP, DCI, or DIND in the LD cohort.iii.The strength of association between LD based CSF-Hb (measured in the morning) and SAH-SBI, aVSP, DCI, and DIND (assessed in the afternoon of the same day) during the first 14 days post-SAH in the LD cohort.iv.The discrimination ability of LD based CSF-Hb (measured in the morning) for SAH-SBI, aVSP, DCI, and DIND (assessed in the afternoon of the same day) during the first 14 days post-SAH in the LD cohort.v.The discrimination ability of LD based CSF-Hb (measured in the morning) for the first occurence of SAH-SBI, aVSP, DCI, and DIND (assessed in the afternoon of the same day) during the first 14 days post-SAH in the LD cohort.vi.The discrimination ability of LD based CSF-Hb (measured in the morning of day X) for the first occurence of SAH-SBI, aVSP, DCI, and DIND (assessed in the afternoon of day X + 1) during the first 14 days post-SAH in the LD cohort.vii.The discrimination ability of LD based CSF-Hb (measured in the morning) for SAH-SBI, aVSP, DCI, and DIND (assessed in the afternoon of the same day) during day 4 and day 14 post-SAH in the LD cohort.EVD based CSF-Hb and 3-months follow-up status:i.The strength of association between EVD based CSF-Hb during the first 14 days post-SAH and chronic hydrocephalus at 12 weeks follow-up in the EVD cohort.ii.The strength of association between EVD based CSF-Hb during the first 14 days post-SAH and functional outcome (GOSE, mRS) at 12 weeks follow-up in the EVD cohort.LD based CSF-Hb and 3-months follow-up status:i.The strength of association between LD based CSF-Hb during the first 14 days post-SAH and chronic hydrocephalus at 12 weeks follow-up in the LD cohort.ii.The strength of association between LD based CSF-Hb during the first 14 days post-SAH and functional outcome (GOSE, mRS) at 12 weeks follow-up in the LD cohort.

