#### Secondary endpoints

Secondary endpoints, which will be assessed during the first 14 days post-SAH on a daily basis, are: angiographic vasospasms (aVSP), delayed cerebral ischemia (DCI), delayed ischemic neurologic deficits (DIND), elements of triple H therapy, spasmolysis, surgical decompression.

The definition of aVSP comprises a narrowing of cerebral arteries based on a DSA, CTA or MRA. In the absence of an appropriate imaging procedure on the respective day, this will be noted as *no imaging performed*. Categorical variable [present, absent or no imaging performed].

DCI is defined as new perfusion deficit or new infarction in native and/or contrast-enhanced CT/MRI. In the absence of an appropriate imaging procedure on the respective day, this will be noted as *no imaging performed*. Categorical variable [present, absent or no imaging performed].

DIND is defined as a new focal neurological deficit or a decrease in GCS of at least 2 points for at least 2 hours. In case the patient cannot be clinically assessed (e.g., sedation), this will be noted as *non-assessable*). Categorical variable [present, absent or non-assessable].

Secondary endpoints, which will be assessed at the 12 weeks (+/− 2 weeks) follow-up: Chronic hydrocephalus, Glasgow Outcome Scale Extended (GOSE), modified Rankin Scale (mRS).

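### Imaging on clinical indication selects the days on which aVSP and DCI are known, so their CSF-Hb cut-offs and toxicity ranges can be systematically biased, not only more variable

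*Protocol article*

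**What the plan says.** Under Secondary endpoints, aVSP and DCI each have three levels: "Categorical variable [present, absent or no imaging performed". A day without suitable imaging is neither present nor absent: "In the absence of an appropriate imaging procedure on the respective day, this will be noted as" a separate category. DIND needs no imaging: "DIND is defined as a new focal neurological deficit or a decrease in GCS of at least 2 points for at least 2 hours". It has its own category for patients who cannot be assessed, for example under sedation.

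The Discussion explains the imaging policy. "In this study, a timed imaging protocol was deliberately avoided", because of radiation and transport risk, and because "it would not have been a compelling substitute for clinically indicated imaging in the setting of neurologic deterioration". It gives the statistical consequence in one clause: "we follow the real clinical situation with imaging according to clinical indication, which increases the variability of the results, but also their generalizability".

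The Secondary objectives (EVD cohort item iv, with parallel items for first occurrence, next-day occurrence, days 4 to 14 and the LD cohort) include "The discrimination ability of EVD based CSF-Hb (measured in the morning) for SAH-SBI, aVSP, DCI, and DIND". The Discussion says ROC analyses of SAH-SBI and of each component will inform the toxicity range, a possible intervention threshold and the development of haptoglobin. It also says that the strict separation of the three component definitions "empowers conclusions regarding CSF-Hb toxicity range and intervention thresholds".

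**The concern.** Whether aVSP or DCI is known on a given day is a clinical decision, and the only trigger the article names is close to the definition of DIND. If DIND rises with CSF-Hb, as the study expects, imaged days carry higher CSF-Hb than unimaged days, among true non-events as well as true events. This is partial verification bias. It moves sensitivity and specificity at a given cut-off, and so the cut-off itself. More patients do not remove it.

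The study wants a marker for daily monitoring of everyone with a drain. ROC results from imaged days answer a narrower question: discrimination among patients for whom someone already saw a reason to image. An aVSP or DCI cut-off that is too high would miss more events than reported. The aVSP and DCI ranges also rest on different days from the DIND range, so a difference between them can partly reflect who was imaged.

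**Working it through.** **1. When a cut-off shifts.** Let h be CSF-Hb, v the true aVSP state and π(h, v) the probability of imaging. On imaged days the density of h is f(h | v)·π(h, v) / E[π | v]. If π does not depend on h once v is given, π cancels and sensitivity, specificity and the Youden cut-off are unchanged. Selection on the outcome alone is harmless here. The cut-off moves only if imaging depends on CSF-Hb among days with the same true aVSP state.

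**2. Does the article's own picture meet that condition?** Imaging follows deterioration, roughly DIND. Suppose DIND were unrelated to CSF-Hb given aVSP. With a = P(aVSP | DIND) and b = P(aVSP | no DIND), mixing the two CSF-Hb distributions gives

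AUC(DIND) = 0.5 + (a − b)·[AUC(aVSP) − 0.5].

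The pilot values in the Background are 0.89 (0.82-0.93) for aVSP and 0.89 (0.84-0.92) for DIND.
- Point estimates: a − b = 0.39/0.39 = 1, so aVSP and DIND would have to fall on exactly the same days.
- DIND at its lower limit: 0.34/0.39 = 0.87.
- aVSP also at its upper limit: 0.34/0.43 = 0.79.

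The Discussion treats the two as distinct, with different ranges. The pilot figures therefore favour a direct DIND to CSF-Hb link, although the article does not say which days they rest on.

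**3. Size, under assumptions.** The article gives no imaging rates or daily prevalences. Assumed: 600,000 independent patient-days; standard normal CSF-Hb; aVSP (20% of days) and DIND (15%) from probit models with AUC 0.89; residual correlation 0 or 0.5; imaging dependent on DIND only. The cut-off maximises sensitivity + specificity − 1. Over all days it is about 0.40 SD above the mean, with sensitivity 0.83.

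| Imaging on DIND / other days | Cut-off, unimaged days dropped | True sensitivity over all days |
|---|---|---|
| 60% / 30% | 0.47-0.55 SD | 0.77-0.80 |
| 80% / 20% | 0.55-0.68 SD | 0.71-0.77 |
| 80% / 10% | 0.62-0.81 SD | 0.64-0.74 |

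Apparent sensitivity on imaged days stays at 0.82-0.84 and the AUC at 0.87-0.90, so neither would reveal the shift. At worst, missed events rise from 1 − 0.83 = 17% to 1 − 0.64 = 36%.

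**4. Does the handling rule matter?** Counting unimaged days as absent still gives 0.48-0.68 SD.

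**5. Other imaging patterns.** A second model used binormal CSF-Hb, aVSP AUC 0.89, aVSP on 10-30% of days and imaging on 90% of DIND days. Shifts are in SD of CSF-Hb within event-free days, a different unit from step 3.

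| Imaging pattern | Shift, unimaged days dropped |
|---|---|
| DIND-driven, 40% of other days imaged | +0.14 to +0.20 |
| DIND-driven, 20% of other days | +0.24 to +0.37 |
| DIND-driven, 5% of other days | +0.46 to +0.68 |
| Unrelated to CSF-Hb, or driven only by true aVSP | about 0 |
| DIND-driven plus routine imaging on low-Hb days | −0.27 to +0.05 |
| Low-Hb days only | about −0.7 |

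In the three DIND-driven rows the AUC is 0.85-0.91 if unimaged days are dropped. If they are counted as absent it is 0.89-0.95, and the shift is +0.14 to +0.41.

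**6. Comparing components.** Return to the model of step 3 with both prevalences at 20%, so that aVSP and DIND share a true cut-off of about 0.40 SD. Imaged days put aVSP at 0.48-0.84 SD, while DIND stays near 0.40 SD even when restricted to the same imaged days, because selection on DIND alone does not move DIND's own cut-off. Comparing on days when all three components are known therefore does not cure the problem. Weighting each imaged day by 1/π returns aVSP to 0.36-0.46 SD.

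**The case against.** - **The article does not say that unimaged days are dropped.** This is correct. It sends secondary analyses to an SAP that is not shown, and the SAP may settle the rule. A reader might infer dropping from the three-level coding, but the documents do not state it. The point does not need it, since both simple rules shift the cut-off under deterioration-driven imaging.
- **The upward direction is not established.** A reader might conclude that the cut-offs will come out too high. The documents do not support that. Deterioration is one named setting and not declared the only one, sedated patients without an assessable DIND are imaged for other reasons, and step 5 shows nil and negative shifts. CSF-Hb is measured only after the last patient's monitoring, so the value itself cannot prompt imaging.
- **No cut-off rule is named.** Youden is an assumption here. The Discussion says a final threshold will also weigh the burden and cost of false results, and the listed objectives concern discrimination, where the AUC changes little. That limits the point to cut-offs and ranges, but the article does promise a toxicity range from these ROC analyses.
- **Increasing ranges across the components.** That phrase describes the pilot, and no listed objective orders the components. If the ranges are read as rising from aVSP to DIND, the simulated bias works against that order. So the documents do not show the ordering to be an artefact, nor that the ranges can never be compared. DIND also has its own unassessable days.
- **The simulation is limited.** DCI was not simulated, and repeated days within patients were treated as independent.

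What stands is that the Discussion presents a possible systematic bias as variability alone, and builds threshold conclusions on the results.

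**Conclusion.** The point holds in a conditional form. Because aVSP and DCI are known only on clinically chosen days, and the named reason overlaps a CSF-Hb-associated endpoint, their ROC cut-offs and toxicity ranges can be biased. If deterioration drives imaging, the bias is probably upward: from about 0.40 SD to between 0.47 and 0.81 SD in the step 3 settings with unimaged days dropped, with little trace in the AUC. The size rests entirely on assumed imaging rates, prevalences and a Youden rule. The direction rests on deterioration being the main trigger.

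The primary test of the composite is not challenged, and the article makes no confirmatory claim from secondary analyses. The change should still be made, because these secondary results are meant to inform thresholds and drug development.

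**What to change.** 1. In the Discussion's imaging paragraph, say that imaging by indication selects the days on which aVSP and DCI are known and may bias their cut-offs.
2. Label unweighted aVSP and DCI ROC results as *among imaged days*.
3. Add a sensitivity analysis for these ROC analyses (EVD and LD cohorts). Model the daily probability of imaging from DIND status (including non-assessable), day post-SAH, site and baseline grades. Use recorded co-interventions only if they precede the imaging, since spasmolysis or triple H therapy may be a response to its result. Weight each imaged day by the inverse of that probability and bootstrap by patient.
4. Order the aVSP, DCI and DIND ranges against one another, or base thresholds on such an ordering, only on the weighted results.

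The cost is wording and modest analysis, with no new imaging, patients or data. Intervals will widen. The correction assumes that imaging depends only on recorded variables. Transcranial doppler, which the Background calls widely used, is not in Table 1, so some selection may remain and should be acknowledged.
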